### 3.1 STUDY OUTCOME MEASURES

Outcomes data to be collected & analysed during the interrupted time-series design:

- Incidence of AKI
- Magnitude of acute deterioration in Creatinine, eGFR
- Compliance with AKI checklist
- Mortality
- Morbidity – secondary complications including other organ failures
- LOS
- Requirement for renal replacement therapies
- Requirement for escalation to critical care

## 4. PARTICIPANT ENTRY

### 4.1 PRE-REGISTRATION EVALUATIONS

No additional tests will be performed in the study compared to if the patient was not in the study.

### 4.2 INCLUSION CRITERIA

Phase 1 – retrospective validation study: adult patients admitted to the Acute medical units of Chichester and Worthing and Becket ward.

Phase 2 - adult patients admitted to the Acute medical units of Chichester and Worthing and Becket ward.

### 4.3 EXCLUSION CRITERIA

Patients admitted to non-Patienttrack wards at WSHT such as delivery suite, day surgery & paediatrics

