| OUTCOME MEASURES | 

• Incidence of Acute Kidney Injury (AKI)

• Magnitude of acute deterioration in Creatinine, eGFR

• Compliance with AKI checklist

• Mortality

• Morbidity – secondary complications including other organ failures

• Length of stay

• Requirement for renal replacement therapies

• Requirement for escalation to critical care

 |
| POPULATION       | Patients admitted to WSHT Acute Medical Units & Becket Ward                                                                                                                                                                                                                                                                                                                                                                           |
| ELIGIBILITY      | All patients over the age of 18 admitted to the Acute medical Units and Becket Ward in WSHT                                                                                                                                                                                                                                                                                                                                           |
| DURATION         | 24 months                                                                                                                                                                                                                                                                                                                                                                                                                             |

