### 3. STUDY DESIGN

2 parallel interrupted time-series design studies, on the Worthing & Chichester sites at WSHT, with segmented linear regression analysis in order to evaluate the longitudinal effect of intervention & controls for trends in outcome.

Initially (Phase 1) we will retrospectively review both sites to validate the score. Using the Chichester site this will add external validity to the APS score.

The alert will then be instituted (Phase 2) at the Worthing site during which time both sites will be monitored for the incidence of Acute kidney injury and adherence to the Patienttrack Assessment Pack at the Worthing site. After interim analysis, the plan will then be to roll-out the alert to the Chichester site and further analyses will then be performed.

Worthing and Chichester are relatively close geographically and demographics are similar making the use of the Chichester site as the initial 'control' arm methodologically sound. If there are significant differences in the two populations in terms of AKI incidence and outcomes, they will be picked up in the initial Phase 1 part of the study

Duration: 24 months

Cohort: All medical patients admitted as emergencies to WSHT two sites Acute Medical Units (AMU) and Becket ward and spend at least one night as an in-patient.

**Baseline data collection:** data will be retrieved from the Patienttrack, Pathology & PAS databases relevant to the 'AKI Patienttrack Assessment Pack'. This data will be transferred to an excel spreadsheet and then anonymised. This data will be stored on the WSHT server & only hospital password protected computers will be able to access this data. Anonymised data for mathematical & statistical analysis will be transferred by password protected & encrypted memory sticks or secure NHS e-mail.

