**Introduction of 'AKI Patienttrack Assessment Pack' to WSHT:** every night PAS will be searched for relevant AKI score diagnosis on every new admission within the last 24hrs & this will be fed into the 'AKI' algorithm. Biochemistry will similarly be searched for the worst eGFR in the last 6/12 to identify the diagnosis Chronic kidney disease (CKD) for the AKI score. RR & AVPU will be fed directly from Patienttrack into the algorithm. Therefore we will be able to identify those patients 'at risk of AKI' who have been admitted within the last 24 hours & this will be displayed using a traffic light system on the patient chart within the AKI Patienttrack Assessment Pack. In addition real time Creatinine results will be fed into the AKI Patienttrack Assessment Pack to highlight 'confirmed AKI' using the same traffic light system. This is demonstrated pictorially below:

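### Eligibility excludes by ward type only, so maintenance-dialysis patients sit in both phases and can be counted in the renal replacement, AKI and creatinine outcomes

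*Protocol*

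**What the plan says.** Section 4.3 consists of one line: "Patients admitted to non-Patienttrack wards at WSHT such as delivery suite, day surgery & paediatrics". Section 4.2 gives the same population for the two phases: "Phase 1 – retrospective validation study: adult patients admitted to the Acute medical units of Chichester and Worthing and Becket ward" and "Phase 2 - adult patients admitted to the Acute medical units of Chichester and Worthing and Becket ward". The Study Summary agrees: "All patients over the age of 18 admitted to the Acute medical Units and Becket Ward in WSHT". Section 3 narrows the cohort only to emergency medical admissions staying at least one night: "All medical patients admitted as emergencies to WSHT two sites Acute Medical Units (AMU) and Becket ward".

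The outcome lists (Study Summary, section 1.1 and section 3.1) include "Requirement for renal replacement therapies", with no restriction to treatment started during the admission. For the alert, section 3 states that "real time Creatinine results will be fed into the AKI Patienttrack Assessment Pack to highlight 'confirmed AKI' using the same traffic light system". The worst eGFR over six months is also looked up, but only to assign CKD as an input to the score.

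Dialysis is mentioned once, in the background, where a published surgical risk index is described. It does not appear in eligibility, the algorithm or the outcome definitions.

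**The concern.** A patient on long-term dialysis who is admitted to an Acute Medical Unit with another illness meets every stated criterion. Three parts of the study are then affected.

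- **Renal replacement.** Dialysis that was already in place can be counted as an outcome, and the alert cannot prevent it.
- **AKI and creatinine/eGFR.** Creatinine moves between dialysis sessions for reasons other than new injury. With no stated filter, such changes may be read as AKI or as acute deterioration.
- **At-risk group and APS validation.** These patients would usually receive the CKD component, so they may cluster among those flagged at risk, the group named in the first Phase 2 aim. In Phase 1 (section 7), AUC and Hosmer-Lemeshow compare patients with and without AKI within seven days, a status with little meaning on maintenance dialysis. If labelled AKI, they can inflate discrimination. If labelled non-AKI, they can lower it.

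**Working it through.** The protocol states no figure that depends on this point, so there is nothing to reproduce. The calculations below show scale only.

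**Inputs**
- From section 2.3: 95 patients developed AKI during admission and 1,219 did not, so 95 / (95 + 1,219) = 95/1,314 = 7.2%, which agrees with the stated 7%.
- Assumed, because the documents are silent: d, the share of admissions on maintenance dialysis (0.25% to 2%); r, the rate of new renal replacement in the other patients (0.2% to 1%); f, the fraction of dialysis patients flagged as AKI (25% to 100%).

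**1. Renal replacement, if every dialysis patient is counted**

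Share of counted patients who were already on dialysis = d / (d + (1 − d)r). A true 30% relative reduction in new treatment appears as 30% × (1 − that share).

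| d | r | already on dialysis | 30% seen as |
|---|---|---|---|
| 0.25% | 1% | 0.0025/0.012475 = 20.0% | 24.0% |
| 0.5% | 0.5% | 0.005/0.009975 = 50.1% | 15.0% |
| 2% | 0.2% | 0.02/0.02196 = 91.1% | 2.7% |

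The result follows the assumptions closely. Below the range, at d = 0.1% and r = 1%, the share is 0.001/0.01099 = 9.1% and the reduction shows as 27.3%. If only half of the dialysis patients are counted, d is replaced by d/2 in the first term: at d = 0.5% and r = 0.5% the share is 0.0025 / (0.0025 + 0.004975) = 33.4%, and the reduction shows as 20.0%.

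**2. AKI incidence**

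Observed incidence = (1 − d) × 7.23% + d × f.
- d = 0.25%, f = 25%: 7.27%, with 0.9% of counted cases from dialysis patients. A 30% reduction shows as 30% × 0.991 = 29.7%.
- d = 2%, f = 100%: 9.09%, with 22.0% from dialysis patients. A 30% reduction shows as 30% × 0.780 = 23.4%.

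**3. What a stable share does in segmented linear regression**

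A constant d adds a constant to each site's series. The absolute step is multiplied only by (1 − d), so the dilution is in the relative effect. Precision also suffers. At d = r = 0.5% the counted proportion is 0.9975% instead of 0.5%, so the binomial variance ratio is (0.009975 × 0.990025) / (0.005 × 0.995) = 1.985, and the standard error of each point rises by a factor of √1.985 = 1.41.

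**4. What a changing share does**

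With r fixed at 0.5% and no alert effect, a move in d from 0.5% to 1% takes the counted rate from 0.005 + 0.995 × 0.005 = 1.00% to 0.01 + 0.99 × 0.005 = 1.50%. If that coincided with the introduction of the alert, it would look like harm. A fall in d would look like benefit.

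**The case against.** - **Reading of the outcome.** A reader might infer that every dialysis patient meets the renal replacement outcome automatically. The text does not support that. Section 1.1 lists the outcome among things the alert may affect, and objective 2b ties harm to unrecognised confirmed AKI, so a requirement arising from AKI is a natural reading. A one-night stay need not include a dialysis session. This stands: the wording allows the count but does not force it. An analysis plan could limit the outcome to new treatment, but that would leave the AKI, creatinine/eGFR and validation problems.
- **Confirmed AKI.** No creatinine criterion is given and the screen figures are not shown, so whether dialysis-related changes would trigger the status cannot be checked. This stands, and the point is put as a possibility.
- **Prior exclusions.** The section 2.3 flow chart is not shown, and 1,561 − 1,219 − 95 = 247 audit patients are unaccounted for in the text. The derivation cohort may have had exclusions. These would not be eligibility criteria for the present phases.
- **Site differences.** A reader might infer that unequal dialysis numbers at Worthing and Chichester bias the comparison. The design is two parallel interrupted time series, so a stable difference is absorbed by each site's own pre-period. This stands.
- **Size.** A reader might infer that prevalent dialysis makes up most of the renal replacement outcome. That follows only from chosen values of d and r. Nothing in the documents says how many dialysis patients these units receive.

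**Conclusion.** The point holds as a defect in the stated eligibility rule, and it should be corrected. Sections 4.2 and 4.3 place maintenance-dialysis patients in both phases, where they can enter outcomes the alert cannot change and a validation in which AKI status has little meaning for them.

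The main consequence is dilution, potentially large for renal replacement and smaller for AKI incidence. Under the assumed ranges, a 30% relative reduction would show as 24% down to 3% for renal replacement and as about 30% down to 23% for AKI. These figures are illustrative: d, r and f are all assumptions, and the renal replacement range takes the least favourable reading of the outcome. The time series is biased only if the dialysis share changes over time. The documents do not establish that contamination is certain, that it dominates any outcome, or that a fixed difference between sites distorts the result.

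**What to change.** Add to section 4.3, for the analysis cohorts: *Patients receiving maintenance dialysis before the index admission are excluded from the APS validation and from the AKI, creatinine/eGFR and renal replacement analyses; the same rule applies at both sites and in all periods.* In the Study Summary, section 1.1 and section 3.1, reword the outcome as *new requirement for renal replacement therapy*.

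This is a filter on the analysis data and changes no patient's care. It needs one added PAS dialysis code at extraction: the data-flow diagram in section 3 lists only liver failure, CCF and diabetes as coded diagnoses, and worst eGFR alone does not separate dialysis from advanced CKD. The remaining costs are a slightly smaller denominator and some misclassification where coding is missing. Reporting the number excluded by site and period would show whether the share was stable.

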### 4.4 WITHDRAWAL CRITERIA

Not applicable

## **5. ADVERSE EVENTS**

This study involves observational analysis initially with no alteration to usual care. When the Acute Kidney Injury Alert and Patienttrack Assessment Packs are introduced at the Worthing site this will constitute a care bundle of best practice advice that should not impact in any adverse way.

The Chief Investigator and the Study team will meet at least monthly to review the data and perform interim analysis of the results.

## **6. ASSESSMENT AND FOLLOW-UP**

This is an initial in-patient study with no long-term follow-up planned outside of normal protocols.

The study ends on the patients discharge.

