### **Research Question/ Main Aims:**

Phase 1 – is the APS externally valid? We will assess this by retrospective external validation of the score on the Chichester site.

Phase 2 - can the use of an electronic prediction & identification alerting tool to deliver an individualised care bundle for hospital in-patients at risk of or with confirmed AKI reduce:

1. The incidence of AKI in those patients 'at risk'
2. The harm (mortality, morbidity, Length of stay (LOS)) associated with failure to recognise those patients with confirmed AKI

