### **Main benefits & potential impact to NHS:**

1. Health benefits immediate & projected medium to longer term
2. Cost-benefit analysis

The trial will be conducted in compliance with the principles of the Declaration of Helsinki 6th revision, the principles of ICH-GCP and all applicable regulatory requirements. The protocol is to be submitted for approval by a Research Ethics Committee.

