## **1.2 RATIONALE FOR CURRENT STUDY**

As the 2009 NCEPOD report highlighted, AKI is a common medical complication that is often diagnosed late and in many cases predictable and avoidable. From our own Worthing Hospital Audit data over six months through the Acute Medical Unit, AKI on admission to hospital had a prevalence of 11%. In addition, 7% of patients subsequently developed AKI during admission. Overall mortality for this combined group of patients with AKI was 19-20%.

Our innovative scoring system - the **Acute Kidney injury Prediction Score (APS)** - utilising physiological measurements, biochemical parameters and known co-morbidities can identify patients at risk of developing AKI following hospital admission. This can then deliver near real-time alerts to nursing and medical staff and will advise on a care bundle.

We would like to retrospectively externally validate the scoring system at another site to add methodological rigor. We will use two parallel interrupted time-series studies, on the Worthing & Chichester sites at WSHT, with segmented linear regression analysis in order to evaluate the longitudinal effect of intervention (use of the score and subsequent alert) and controls for trends in outcome.

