## **7. STATISTICS AND DATA ANALYSIS**

Logistic regression analysis will be used to identify predictors of development of acute kidney injury within seven days of admission. The scoring system (APS) developed from a previous Logistic regression analysis will be re-evaluated. The calibration of the scoring system will be assessed by the Hosmer-Lemeshow goodness-of-fit test. Discrimination will be assessed using the area under the receiver operating characteristic curve (AUC). Validation will be carried out by applying the scoring system comparing patients with AKI and those who did not develop AKI within 7 days.

Statistical analyses will be performed using SPSS v.19 with P-values below 0.05 considered as significant.

Data and all appropriate documentation will be stored for a minimum of 10 years after the completion of the study, including the follow-up period – as per MRC Good Research Practice Guidelines (2005).

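### Phase 2 mortality, and less strongly hospital-acquired AKI, is counted only until discharge, so a change in length of stay that starts with the alert would move both rates without a true effect

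*Protocol*

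**What the plan says.** Protocol Section 6 describes follow-up in two sentences: "This is an initial in-patient study with no long-term follow-up planned outside of normal protocols" and "The study ends on the patients discharge".

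The Phase 2 aims (Research Question/Main Aims, repeated in Section 2.1) are to reduce "The incidence of AKI in those patients 'at risk'" and "The harm (mortality, morbidity, Length of stay (LOS)) associated with failure to recognise those patients with confirmed AKI". Section 3.1, which opens with "Outcomes data to be collected & analysed during the interrupted time-series design", lists AKI incidence, mortality and length of stay side by side and gives none of them a time window. The audit table in Section 2.3 heads its death rates as hospital mortality.

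The only fixed window in the protocol is in Section 7: AKI within seven days of admission. It is written for the logistic regression and validation of the score, not for the Phase 2 time series. Section 3 defines the cohort as emergency medical admissions staying at least one night, so stays shorter than seven days are included.

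**The concern.** A death or a new AKI can be recorded only while the patient is in hospital. Each patient's observation time is then the length of stay, and length of stay is one of the quantities the intervention is intended to change. If patients leave sooner after the alert is introduced, some deaths and AKI episodes that would have been counted before now fall outside the count. If closer monitoring keeps patients in longer, more events are counted and a real benefit can be hidden.

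The protocol relies on segmented regression and on Chichester as a parallel control. These deal with trends already present before the alert and with changes shared by both sites. They do not deal with a change in stay that begins at Worthing when the alert begins, because that change falls on the breakpoint at which the effect is estimated. If the alert is then rolled out at Chichester, the same artefact could recur there and look like replication. Adjusting for length of stay is no remedy, since it is itself affected by the alert.

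This is not a detail that can be left to an analysis plan. Section 6 fixes when observation ends, and data never extracted cannot be analysed later.

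**Working it through.** **Inputs from the protocol (Section 2.3, with Section 1.2)**
- AKI on admission: 184 patients.
- Hospital-acquired AKI: 95 patients; 1219 did not develop it.
- Hospital mortality in AKI patients: 19% to 20%; the midpoint 19.5% is used below.
- Length of stay: not given anywhere.

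**Reproducing the baseline.** 95/(1219 + 95) = 95/1314 = 7.2%, which agrees with the stated 7%. The death rates cannot be reproduced because no death counts are given.

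**Share of AKI that stay cannot affect.** 184/(184 + 95) = 184/279 = 66% of the audit's AKI cases were present on admission. The problem concerns the remaining 95 and the deaths.

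**Illustration.** Assume a constant daily event risk h in hospital and a constant daily discharge rate 1/L. L is the assumed mean stay (strictly, the mean time to discharge if no event intervenes). The proportion with the event before discharge is

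p = h / (h + 1/L), so h = [p/(1 − p)]/L.

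Hold h fixed and replace L by L − 1. For mortality with L = 10: h = (0.195/0.805)/10 = 0.0242, and the new rate is 0.0242/(0.0242 + 1/9) = 17.9%.

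| Assumed L | Hospital mortality in AKI patients | Hospital-acquired AKI, counted to discharge | Hospital-acquired AKI, 7-day cap, still seen only in hospital |
|---|---|---|---|
| 5 days | 19.5% → 16.2% (−17%) | 7.2% → 5.8% (−19%) | 7.2% → 6.3% (−12%) |
| 7 days | 19.5% → 17.2% (−12%) | 7.2% → 6.2% (−13%) | 7.2% → 6.7% (−7%) |
| 10 days | 19.5% → 17.9% (−8%) | 7.2% → 6.5% (−9%) | 7.2% → 7.0% (−3%) |

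Percentages in brackets are relative changes. In the last column p = [h/(h + 1/L)] × [1 − exp(−7(h + 1/L))], with h recalibrated so that the baseline is again 7.2%.

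**Opposite direction.** One day longer, same formula with L + 1: for L = 5, h = 0.0484 and 0.0484/(0.0484 + 1/6) = 22.5%, a relative rise of about 15% in counted deaths with no change in daily risk.

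**Fixed window.** Under the same assumptions, death by day 30 is 1 − exp(−30h). It does not contain L, so a change in discharge alone cannot move it.

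**Limit of the model.** Carried past discharge, even the lowest of these risks gives 1 − exp(−30 × 0.0242) = 52% dead by day 30, against 19.5% in hospital. Nothing in the protocol supports that. The figures show the direction and a plausible order of size; they are not an estimate.

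**The case against.** The strongest reply is that the size is unsupported. Stay is assumed, and the constant risk implies far more deaths after discharge than the documents warrant. If the patients who leave earlier are mainly those who have recovered, in-hospital mortality hardly moves. This stands as a limit on size. It does not remove the dependence on stay.

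The AKI part is weaker than the mortality part. Most audit AKI was present on admission, and a seven-day window, if carried into Phase 2, would shrink the artefact. This also stands.

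Length of stay is itself analysed, so a shift would be visible. That would warn the reader, but it would not say how much of a fall in mortality was due to the shift.

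Four stronger readings are tempting, and the documents do not support them.
- *That the alert would necessarily appear to reduce AKI and deaths.* Stay might lengthen. The checklist also asks for daily creatinine, which could raise AKI detection. The net direction is unknown. A trend in stay that predates the alert or is shared by both sites is addressed by the design.
- *That the protocol contradicts itself on the AKI window.* The statement "In addition, 7% of patients subsequently developed AKI during admission" describes a past audit, whereas the seven-day window belongs to a planned analysis.
- *That Phase 1 counts early-discharged patients as free of AKI.* Section 7 says "Validation will be carried out by applying the scoring system comparing patients with AKI and those who did not develop AKI within 7 days" but does not say how they are classed. In the audit, 1561 − 1219 − 95 = 247 patients are not accounted for in the text. The flow chart, which is not shown, may explain them, possibly as exclusions.
- *That the protocol claims to measure long-term benefit.* The phrase "Health benefits immediate & projected medium to longer term" concerns projected impact on the NHS and is not a study outcome.

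**Conclusion.** The point holds in a limited form. Because Section 6 ends observation at discharge, Phase 2 mortality is in-hospital mortality and depends on length of stay, an outcome the alert aims to reduce. Hospital-acquired AKI shares the weakness to a lesser degree; AKI on admission does not. A change in stay confined to Worthing and starting with the alert would bias the comparison in either direction, and the planned analysis has no means of removing it.

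The protocol does not allow the bias to be sized. The relative artefact of about 8% to 17% in hospital mortality among AKI patients rests on assumed mean stays of 5 to 10 days, discharge one day earlier, and a daily risk that is constant and unaffected by discharge. It is smaller if events cluster early in the stay or if mainly recovered patients leave sooner. No single figure within that range should be quoted as the expected bias. The point should be addressed because the remedy is cheap and linkage may be lost once the data are anonymised.

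**What to change.** Amend Section 6, and Section 3.1 to match.

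1. Define mortality as death within a fixed window from admission (for example 30 days), wherever it occurs, identical at both sites and in all periods. Obtain it by linkage to routine records before anonymisation.
2. Keep in-hospital death as a secondary outcome, labelled as such.
3. Report hospital-acquired AKI within 7 days of admission separately from AKI on admission. Use any creatinine in the Trust pathology database, including samples taken after discharge. State that ascertainment after discharge is incomplete, because a result exists only where someone retested. This part of the remedy is partial.

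Restricting the validation to AKI cases plus non-cases tested to day 7 is not advised, because it selects on the outcome and can distort the AUC.

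**Cost.** Extraction must wait until 30 days after the last admission. No patient contact or additional test is needed. The sponsor must confirm that PAS or another linked source holds deaths after discharge; the protocol shows PAS supplying only age and coded diagnoses to the algorithm. It must also confirm that approvals cover the linkage, since Section 8.2 relies on ward posters and Section 2.2 describes capture of the in-patient episode. Some out-of-area deaths and tests will be missed.
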